## **Sample**

### Quantitative:

CR-indicated population (Obj 1): To compute CR need, the most current estimates of annual incidence of IHD will be extracted from the GBD by country. IHD is typically due to narrowing of the coronary arteries, usually due to atherosclerosis. GBD estimates IHD as the aggregate of discrete atherosclerosis sequelae, namely: myocardial infarction, angina, or ischemic cardiomyopathy (heart failure due to IHD). In GBD, for IHD, myocardial infarction is defined as per the Fourth Universal Definition, and coronary artery disease is defined as at least moderate (>50%) stenosis of an epicardial coronary vessel based on angiographic or functional diagnostic testing. Ischemic HF is diagnosed clinically using the Framingham or European Society of Cardiology criteria.

Based on internationally-agreed guidelines (see Table 2 here), IHD and HF are the main diagnoses indicated for CR, thus this represents the number of patients who would be indicated for CR in a given year. Note that non-ischemic HF patients are also indicated for CR, but no reliable and comparable source of incidence was available in all countries. Therefore, the estimate of CR need should be considered under. Note evidence suggests patients with valve procedures, rhythm issues, or other vascular conditions (e.g., peripheral arterial disease, stroke) also benefit from CR, but these patients were not considered in the estimate of CR need herein. So again, the CR-indicated population is under-estimated, but is as reliable as available.

### CR Program Sample (Obj 1-3):

The population consists of all phase 2 (as defined in North America) CR programs identified in the world. The sample will consist of all identified, consenting programs in the world. The most responsible clinician of the identified CR programs will be asked to complete the survey.

*CR Program Inclusion Criteria:* Post-acute care CR programs offering at least: (i) initial assessment, (ii) structured aerobic exercise (can be supervised or unsupervised; e.g., remote via technology) and (iii) at least one other component to control CV risk factors (e.g., patient education, psychosocial or dietary counselling, tobacco cessation). Setting can be residential, but is generally outpatient.

*Exclusion Criteria:* Programs that offer CR solely and temporarily as part of a research study. Phase I and maintenance programs.

*Qualitative (Obj 3):*

*Inclusion:* (a) Lead clinicians of existing CR programs, (b) Board members of CR-related societies, and (c) cardiac policy-makers, in countries with the greatest CR service shortfall (e.g., exceeding 250,000 patients per year), lowest CR coverage and/or largest reductions in capacity since the previous Audit will be eligible to participate.

*Exclusion:* Self-reported lack of proficiency in English, and for countries with CR, staff for whom CR is not in their job purview.

While sample size cannot be determined a priori, we are estimating 30 interviews to reach saturation of themes. When no new information is emerging upon concurrent interview coding, data saturation will be considered achieved.

## **Measures**

*Quantitative:*

*Objective 1:*

Countries will be characterized by World Bank income class (i.e., 4) and WHO region (i.e., 6). Surveys without country specified were grouped together separately but maintained in the sample to promote generalizability. The indicators below will be aggregated at the country, region, income class and global analytic levels.

CR need: raw IHD incidence per country from latest Global Burden of Disease estimates (2023; <https://vizhub.healthdata.org/gbd-results?params=gbd-api-2021-permalink/6afc006e91ec18286cf82cec24bc38c1>), minus correction value as described below.

To conservatively take into account that some patients do not survive an incident event (e.g., 30-day survival) to the point of initiating CR or they suffer comorbidities which render them ineligible for CR (inability to ambulate, comorbid terminal condition, comorbid sensory or cognitive impairment), a correction was applied to national incidence values to represent a more true CR-eligible population estimate. Based on the literature showing inequality in CVD morbidity and mortality, we assumed that 85% of incident IHD patients in HICs would be eligible for CR, 80% in MICs, and 75% in LICs.

CR availability: existence of  $\geq 1$  program in a country (yes/no), with the total number of available programs ascertained by the national champions.

CR capacity refers to the number of patients a program reports they could serve annually. For each program, total capacity was computed as the sum of annual supervised and unsupervised capacity. For programs that offered either CR model but had missing or outlier (i.e.,  $>10,000$ ) capacity values, the median capacity for the WHO region of the country in which program is located was imputed. However, while not applicable for supervised models given number of responses, if  $<5$  programs within a region reported capacity for unsupervised CR, the overall median unsupervised program capacity across all MICs was applied (i.e., 75), as none of the remaining countries with missing data were classified as HICs and only 2 responding countries were LICs. Zero capacity reflects no availability.

Median program capacity was determined based on the total capacity values across all programs within that country. This was then multiplied by the number of programs in the country to ascertain national CR capacity.

CR service shortfall(-)/surplus(+): CR capacity (national, regional, income class, and global) minus need (corrected number of incident IHD patients per year by analytic level). During computation of regional and global CR service levels, the capacity for each country was constrained to its estimated need, thereby avoiding redistribution of over-capacity to other countries in which it could not have been operational. Negative values represent a shortfall, and positive values a surplus. Zero would reflect a balance of need and capacity.

CR coverage: is calculated as  $(\text{capacity} / \text{need}) \times 100\%$ , for each analytic level. During computation of global and regional CR shortfalls, the capacity for each country was constrained to its estimated need, thereby avoiding redistribution of over-capacity to other countries in which it could not have been operational.

Values  $<100\%$  represent under-capacity;  $100\%$  are adequate and  $>100\%$  potential excess capacity (bearing in mind non-ischemic HF and other indicated patient types could not be considered in CR need). Where capacity is zero, coverage =  $0\%$ . Coverage %s were ranked by country (1 best).

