#### Objectives 1-3 (Survey):

Country and program response rates will be computed. SPSS version 31 will be utilized, analyzing all initiated surveys.

The number of responses for each question may vary due to missing data, such as instances where respondents did not answer a question due to legitimate inapplicability or the use of skip logic. For descriptive analyses, percentages will be computed using the number of valid responses for the specific item as the denominator.

Data cleaning was documented in an Audit trail. Given the small CR samples in some countries, except for the CR capacity variable, missing data will not be imputed. For continuous variables, outliers and implausible values were also reviewed and addressed as appropriate.

Descriptive statistics, including frequency with percentage (e.g., mode items) or median with quartiles (e.g., capacity) as appropriate, will be applied to analyze all closed-ended items in the survey. Open-ended items with responses from more than 10% of responding programs will be coded using content analysis.

*Mode of CR delivery:* A descriptive examination of responding program characteristics will be performed. Delivery mode availability will be described by country, and characteristics of hybrid delivery (e.g., technology, dose, comprehensiveness, multidisciplinary) by region and income class. Availability (yes/no) of unsupervised delivery specifically, and where yes capacity (patients served per year) and reimbursement (yes/no) will be compared descriptively to the previous Audits at a country level, with current income class, regional and global summary statistics computed. Regional and income class differences (independent variables) in the above parameters of capacity and reimbursement will be tested in an exploratory manner via generalized linear mixed models (GLMM), to account for clustering of programs, where country is the random effect. The models will be fitted via the Poisson distribution log link function.

*Objective 3 – Access and equity:* Strategies for referral of patients to the CR programs will be described by country, region, and income class, with a focus on eReferral. Barriers to broader delivery will be described in the same manner. Regional and income class differences (independent variables) in referral strategies and barriers (dependent variables) will also be tested each using GLMM as above.

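### Filling missing program capacity with the WHO-region median and then testing regional differences in capacity inflates the false-positive rate of that exploratory test; the same fill can outvote a country's own reports in its national capacity.

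*Protocol*

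**What the plan says.** Under Measures, Objective 1, the rule is triggered by survey data that show a delivery model but no usable capacity: "For programs that offered either CR model but had missing or outlier" values, an outlier being anything above 10,000. For these programs "the median capacity for the WHO region of the country in which program is located was imputed". For unsupervised capacity there is a fallback when fewer than 5 programs in a region report: "the overall median unsupervised program capacity across all MICs was applied (i.e., 75". The protocol justifies it on the ground that no remaining country with gaps is high-income and only 2 responding countries are low-income.

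The values are then aggregated: "Median program capacity was determined based on the total capacity values across all programs within that country". That median times the number of programs in the country is national capacity.

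Under Data Analyses, Objectives 1-3 (Survey), "except for the CR capacity variable, missing data will not be imputed". The Mode of CR delivery paragraph then states: "Regional and income class differences (independent variables) in the above parameters of capacity and reimbursement will be tested in an exploratory manner". The model is a Poisson log-link mixed model, used "to account for clustering of programs, where country is the random effect". No reported-values-only analysis and no allowance for imputation uncertainty is described.

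**The concern.** Region is a country-level attribute, so the yardstick for a regional difference is how much countries differ within a region. The fill gives programs from different countries of one region the same number. This pulls those countries together and shrinks the yardstick. Chance differences between regional medians remain, because each fill is drawn from its own region's reports. The test is therefore biased towards finding a regional difference.

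The capacity in question appears to be that of unsupervised delivery, which is where the protocol itself needed a fallback for thin reporting.

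The second consequence needs no test. Filled values enter the country median on the same footing as reported ones. National capacity feeds shortfall, coverage and country rank, the choice of countries for interviews, and the country summaries sent to Societies for advocacy.

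**Working it through.** **Inputs from the protocol.** 6 WHO regions, so the region test has 5 df. For scale, the first Audit found 111 countries with CR and a median of 4 programs per country (Background). The protocol gives no missing rate, alpha or sample size for this test, so there is no stated figure to reproduce.

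**Assumptions.** Nominal 5% test; missing share m from 5% to 50%; 6 regions of 8 or 18 countries (48 or 108 in all); about 4 programs per country; log-normal capacity around 75; log-scale SD 0.5 or 0.8 between countries and 1.0 between programs; no true regional difference.

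**Step 1: approximation.** If a share m of each country's programs is set to the regional centre, each country's deviation from its region shrinks by (1 − m). The error variance shrinks by (1 − m)², while the variance of the regional centres does not. The F statistic is inflated by 1/(1 − m)², so the true rejection rate is P(F > F_crit × (1 − m)²). With 108 countries there are 5 and 102 df and F_crit = 2.303:

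- m = 0.05: cut-off 2.079, rejection 7.4%
- m = 0.10: 1.866, 10.7%
- m = 0.20: 1.474, 20.5%
- m = 0.30: 1.129, 35.0%
- m = 0.50: 0.576, 71.8%

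**Step 2: simulation under the null.** The fill was applied as the protocol words it. The region test was run as an F test on log country means (1,000 to 2,000 runs per setting) and as a Poisson random-intercept model with a 5-df likelihood ratio test (300 runs per setting). Gaps fell at random or clustered by country.

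| Missing share | Region test after fill (range over set-ups) | Poisson mixed model: after fill | Poisson mixed model: reported only |
|---|---|---|---|
| 5% | 6–7% | – | – |
| 10% | 8–11% | 8.7% | 4.3% |
| 20% | 12–19% | – | – |
| 30% | 22–33% | 29.7% | 5.3% |
| 50% | 53–72% | 61.3% | 7.0% |

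On reported values the F test stayed at 3.5–6.3%. With 300 runs the Monte Carlo standard error at 29.7% is √(0.297 × 0.703 / 300) = 2.6 points. The simulated rates lie near or below step 1, which idealises the gaps as evenly spread over countries.

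**Step 3: the fallback of 75.** With 1 to 3 regions on the fallback, the region test rejected 26–28% at 30% missing and 42–55% at 50%, against 6–10% on reported values. Sparse regions alone lift that comparator above 5%.

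**Step 4: income class.** In the same simulations the income-class test stayed at 4–6%, with or without the fill.

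**Step 5: national capacity (illustrative).** Two programs report 30 and 40, the regional median is 120, and every program in the country returned a survey.

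- One gap: values 30, 40, 120; median 40 rather than 35; national 3 × 40 = 120 against 3 × 35 = 105.
- Two gaps: 30, 40, 120, 120; median 80; 4 × 80 = 320 against 4 × 35 = 140.
- Three gaps: 30, 40, 120, 120, 120; median 120; 5 × 120 = 600 against 5 × 35 = 175.

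**The case against.** The strongest reply is that the protocol never says in so many words that imputed values enter the mixed models. The fill is set out under Objective 1 to build national totals. This stands as a caveat. But the survey analysis section makes capacity the stated exception to no imputation and then tests capacity, so entry of the imputed values is the natural reading.

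Next, the missing rate is unknown, and at 5% to 10% the inflation is modest. The tests are labelled exploratory, and Objective 1 is descriptive. Both points stand and lower the priority. Neither corrects the error rate.

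A reader might infer three stronger claims that the documents do not support:

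- *That a country's own reports are overridden.* Reported values up to 10,000 are kept. They are ignored when gaps are filled, and outvoted only when about half or more of the values are filled.
- *That countries with low response are pulled to the regional value.* The fill covers programs whose survey shows a model but no usable capacity. Programs that never responded are not described as filled; they enter through multiplication by the number of programs. If one of three programs reports 30 and two never respond, the median stays 30 and the total 90. Only if both returned surveys without usable capacity would a regional median of 150 give 150 and 450.
- *That the value of 75 erases a real low- versus middle-income difference.* The protocol reports no such difference, the fallback is confined to unsupervised capacity in thinly reporting regions, and its reason is given. Income-class false positives were not inflated. Loss of power for that contrast was not examined.

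Filling from one or two in-country reporters also trades bias for instability, so that step belongs in a sensitivity analysis.

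**Conclusion.** The concern holds for the region test of capacity and should be fixed. If imputed values enter the model, the nominal 5% level is not kept. The excess is slight at 5% missing, roughly four to seven times nominal at 30% (22–33%), and makes the test uninformative at 50%. These sizes rest on the assumed missing rates and variance components above; the direction follows from the form of the fill.

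The conclusion does not extend to the income-class test, or to reimbursement, referral strategies and barriers, which are not imputed. The effect on national capacity is a separate matter that the exploratory label does not cover. It is material only in countries where about half or more of the responding programs lack a usable value, and the protocol does not say how many these are.

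**What to change.** In Data Analyses, Objectives 1-3 (Survey), state that the capacity mixed models are fitted to reported values only and that imputation is confined to the national totals. Report the share of imputed capacity values by country and by region.

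Add a sensitivity analysis of national capacity, and of the shortfall, coverage and rank derived from it, that fills a gap from the country's own reporting programs first and uses the regional median only where none report. Flag countries whose figure relies on the all-MIC value of 75.

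The cost is a change of wording and a re-run, with no new data. The models lose the filled records, which carried no information on capacity. In-country fills will be unstable where few programs report. In regions with very few reporters, the region test on reported values can itself run above 5% and should be read with that in mind.

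### The cap on each country's capacity is written for regional and global totals but not for income class, so income-class shortfall and coverage follow a different rule whenever any country has capacity above its need

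*Protocol*

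**What the plan says.** Protocol, Measures, Objective 1 sets the reporting levels: "The indicators below will be aggregated at the country, region, income class and global analytic levels". The shortfall/surplus definition then covers all of them: "CR capacity (national, regional, income class, and global) minus need". Coverage is capacity over need, as a percentage, also at each level.

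The cap appears twice. In the shortfall/surplus paragraph: "During computation of regional and global CR service levels, the capacity for each country was constrained to its estimated need". In the coverage paragraph: "During computation of global and regional CR shortfalls, the capacity for each country was constrained to its estimated need". Both give the same reason: "thereby avoiding redistribution of over-capacity to other countries in which it could not have been operational".

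Surpluses are expected to be possible: "Negative values represent a shortfall, and positive values a surplus". The coverage paragraph likewise interprets values above 100%.

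Data Analyses, Objective 1 (GBD) adds no rule of its own. It refers back to these definitions for every level, and plans to describe change since the first Audit by income class and by region together.

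**The concern.** The definition lists four levels, and the cap that follows names two. Leaving out the national level makes sense, because a country's own surplus is meant to show. Leaving out income class does not: a class is a set of separate countries, so the reason given for the cap applies to it just as it does to a WHO region.

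An analyst who follows the text would cap regions and the globe and leave income classes uncapped. Income-class and regional results, presented side by side, would then rest on different rules. A surplus country would offset unmet need elsewhere in its class, and the class totals would not add up to the published global shortfall. A reader would have no means of telling which rule had been used.

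**Working it through.** The Protocol states no coverage or shortfall figure for this Audit, so there is nothing to reproduce. The check compares the two aggregation rules.

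**Formulas.** For country *i* let C be capacity and N corrected need.

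- Uncapped coverage of a group: ΣC / ΣN. Uncapped balance: ΣC − ΣN.
- Capped coverage: Σmin(C, N) / ΣN. Capped balance: Σmin(C, N) − ΣN.
- Since C − min(C, N) = max(C − N, 0), the uncapped balance exceeds the capped one by the sum of the national surpluses in the group. Coverage exceeds it by that sum divided by group need.
- If every country belongs to exactly one income class, the uncapped class balances summed over classes differ from the capped global balance by the sum of all national surpluses.

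**Inputs.** The eligibility corrections of 85%, 80% and 75% for high-, middle- and low-income countries are the Protocol's (Measures, Objective 1). All incidences and capacities below are assumed for illustration, and middle-income countries are taken as one group.

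| Group | Incidence × correction = need | Capacity |
|---|---|---|
| High-income A | 100,000 × 0.85 = 85,000 | 127,500 (150%) |
| High-income B | 100,000 × 0.85 = 85,000 | 34,000 (40%) |
| Middle-income | 400,000 × 0.80 = 320,000 | 32,000 (10%) |
| Low-income | 50,000 × 0.75 = 37,500 | 375 (1%) |

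**High-income class.**

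- Uncapped: 161,500 / 170,000 = 95.0%; balance 161,500 − 170,000 = −8,500.
- Capped: (85,000 + 34,000) / 170,000 = 119,000 / 170,000 = 70.0%; balance −51,000.

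**Reconciliation with the global figure.**

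- The other two classes are the same under either rule: 32,000 − 320,000 = −288,000 and 375 − 37,500 = −37,125.
- Classes as written: −8,500 − 288,000 − 37,125 = −333,625.
- Capped global: (119,000 + 32,000 + 375) − 527,500 = −376,125; coverage 151,375 / 527,500 = 28.70%.
- Gap: 376,125 − 333,625 = 42,500, which is country A's surplus (127,500 − 85,000).
- Need-weighted income-class coverage as written: 193,875 / 527,500 = 36.75%, against 28.70% globally.
- With classes also capped: −51,000 − 288,000 − 37,125 = −376,125, which agrees exactly.

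**Range, varying only country A's coverage.**

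| Country A | High-income coverage, uncapped | Capped | Gap to global shortfall |
|---|---|---|---|
| 100% | 70.0% | 70.0% | 0 |
| 110% | 75.0% | 70.0% | 8,500 |
| 125% | 82.5% | 70.0% | 21,250 |
| 150% | 95.0% | 70.0% | 42,500 |
| 200% | 120.0% | 70.0% | 85,000 |

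In the last row the class shows an apparent surplus of 204,000 − 170,000 = 34,000, although country B meets only 40% of its need.

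**The case against.** The strongest reply is that the Protocol is silent on income class and does not declare it uncapped. The reason it gives is general, so the omission may be a drafting slip, and the past tense suggests an incomplete record of a computation already made. That may be so, and the text does not show what was actually computed. But the Protocol fixes this rule itself, and as written the rule does not reach income class. The reference back in Data Analyses cannot extend it, because capping at every level would also abolish the country surpluses that the plan intends to show.

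A second reply is that surpluses may be rare. The Background reports one place for every 12 new patients in the first Audit and a median national capacity of 120 patients a year. Need has since widened from acute coronary syndrome to ischemic heart disease, which works against surplus. Adding unsupervised capacity and applying the eligibility correction work towards it. The net effect is unknown, so the consequence has to be stated conditionally. The example is also deliberately stark: in a class of many countries, one small surplus country would move coverage little.

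Three stronger readings are tempting but unsupported:

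- That the omission flatters high-income countries and exaggerates the gap to poorer ones. No figure in the Protocol shows where surpluses lie.
- That income class is the main equity comparison. The plan treats region and income class in parallel, and describes access by country too.
- That coverage is never capped at any level, because the second cap sentence opens "During computation of global and regional CR shortfalls". That sentence stands inside the coverage definition and constrains its numerator, so the intent is clear and the wording is a slip.

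**Conclusion.** The point holds in conditional form. The cap as written omits one of the multi-country levels at which shortfall and coverage are reported, and the Protocol's own reason for the cap gives no ground for the omission. If at least one country has capacity above its need, coverage of its income class is overstated relative to the capped rule by that class's national surpluses divided by class need. The class shortfalls then differ from the capped global shortfall by the sum of all national surpluses. This assumes that each country falls in exactly one class.

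The actual size cannot be determined from the Protocol; it is zero if no country exceeds its need. A reader might infer that the income-class results are bound to be wrong. The text does not support that, because it shows neither that a surplus exists nor that the class computation was in fact left uncapped. Country values, coverage ranks, and regional and global results under the intended cap are unaffected, and these comparisons are descriptive, with no inferential test at stake.

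**What to change.** Name income class beside regional and global in both cap sentences. In the coverage paragraph, replace the reference to shortfalls with coverage and give the formula for every multi-country level: the sum of min(capacity, need) over countries, divided by the sum of need. Add that a surplus, or coverage above 100%, can then appear only at country level. Before reporting, check that the regional shortfalls and the income-class shortfalls each sum to the global shortfall.

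If the investigators do want income class uncapped, they should give the reason and warn that those figures need not reconcile with the global one.

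The cost is about one sentence of text and one spreadsheet column; no new data are needed.
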